
Several methods have been suggested to modify and improve the gut microbiota such as probiotic and prebiotic supplementation and fasting [17, 18]. Time-restricted feeding (TRF) is a kind of fasting recommending individuals to confine the eating window to a specified number of hours per day, without altering calorie intake or diet quality [19]. TRF could alter the diversity or abundance of the gut microbiome in response to the body’s circadian rhythm [20]. In turn, gut microbiota can modulate BDNF expression in the brain [21] and also feeding behavior [10]. Feeding behavior can be affected by stress level in individuals and a significant correlation between food addiction and stress has been reported in individuals with overweight and obesity [22, 23]. Lipopolysaccharide (LPS) is an endotoxin produced by altered gut microbiota and is associated with low-grade inflammation in obesity [24, 25]. Lipopolysaccharide-binding protein (LBP) is an acute phase protein produced by the liver which binds to LPS and is a part of LPS-induced inflammation. Serum LBP can be measured to evaluate changes in the gut microbiome [24, 25]. On the other hand, previous clinical trials documented that TRF might have a favorable effect on weight loss, reduction of insulin resistance, systolic blood pressure, and fasting glucose levels [26]. However, some previous studies did not show any advantages of using TRF on body weight management [27, 28]. Therefore, these aforementioned discrepancies may be explainable by ignoring the role of feeding behavior disorders such as food addiction on body weight management. Hence, the aim of this clinical trial is to investigate the effect of TRF on anthropometric indices, stress level, eating behavior, and serum levels of BDNF and LBP in women with overweight/obesity and food addiction.

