### Randomization, sequence generation, and concealment

Participants will be randomly allocated into two groups: the group receiving a low-calorie diet with the time-restricted feeding protocol or the control group receiving a low-calorie diet and will be followed up for 8 weeks. Stratified blocked randomization method is used to randomly assign people to two groups. The sequencing will be generated by one of the authors (AS) who is not going to assign participants into the study, so, allocation concealment will be ensured, as the author will not release the randomization code until the patient has been recruited into the trial by other authors (HI and [name]), which takes place after all baseline measurements have been completed. Participants are classified into overweight (26–29.9 kg/m^2^), grade 1 (30–34.9 kg/m^2^), and grade 2 obesity (35–39.9 kg/m^2^) based on BMI and randomly assigned to one of the control or TRF groups. Separate randomization is performed within each group for each BMI class. The size of the blocks is 4, two allocations are given to TRF group (A) and two allocations to Control Group (B). Six different permutations of AABB, ABAB, BBAA, BABA, ABBA, and BAAB will be created.

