### Assessment of dietary intake

In this study, to assess participant’s dietary intake, at the beginning of the study, at the end of the fourth and eighth weeks of the study, 3 days of dietary recall about one weekend day and two week days will be completed through face-to-face or telephone interviews. Common household measurement tools (glass, cup, soup bowl, plates, teaspoon, and tablespoon) will be provided to assist subjects in estimating the portion size of the food. Dietary intake will be analyzed using Nutritionist IV (N4) software.

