### Statistical analysis

In this study, data analysis will be performed by using SPSS version 21.0 (SPSS Inc, Chicago, Illinois) software. Paired *t* test will be used to compare the mean of quantitative variables with normal distribution in each group between the beginning and the end of the study and the *t* test will be used to compare their mean between the two groups at the beginning and end of the study. In the case of quantitative variables with non-normal distribution, Wilcoxon and Mann-Whitney tests are used, respectively. In case of the variables measured three times during the study (beginning, fourth week, and eighth week), repeated ANOVA test will be used. Covariance analysis will be used to eliminate the effect of quantitative confounding factors. Quantitative confounding factors are physical activity and baseline values of the biochemical markers. Chi-square test will be used to compare the qualitative variables between the two groups and regression analysis is used to eliminate the effect of qualitative confounding.

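### The repeated ANOVA for dietary intake uses the pre-randomisation recall as a response rather than a covariate, which weakens every intake comparison the plan offers and, under one reading, dilutes the difference to two thirds

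*Protocol article*

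**What the plan says.** All references are to the protocol article.

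- **Statistical analysis** sets the method for variables with three measurements: "In case of the variables measured three times during the study (beginning, fourth week, and eighth week), repeated ANOVA test will be used". It does not say which term compares the arms.
- **Assessment of dietary intake** gives the matching schedule: "at the beginning of the study, at the end of the fourth and eighth weeks of the study, 3 days of dietary recall". No other variable has an explicit three-time schedule.
- **Randomization, sequence generation, and concealment** places release of the allocation code after baseline; this step "takes place after all baseline measurements have been completed".
- **Statistical analysis** also plans a comparison for normally distributed quantitative variables in general: "the *t* test will be used to compare their mean between the two groups at the beginning and end of the study". It does not say whether the repeated ANOVA replaces this test for intake.
- On covariance analysis, the same section says: "Quantitative confounding factors are physical activity and baseline values of the biochemical markers". Baseline intake is not on that list.
- **Study outcomes** lists dietary intake as neither a primary nor a secondary outcome.
- **Intervention** applies one calorie-deduction rule to both arms. **Background** describes time-restricted feeding (TRF) as advice to "confine the eating window to a specified number of hours per day, without altering calorie intake or diet quality".

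**The concern.** A value recorded before allocation cannot show an effect of allocation. Its proper use is to explain between-woman variation in the later values, as a covariate. Treated as a third response, it either enters the arm average, where it contributes an expected difference of zero, or serves as the reference for a 2-degree-of-freedom interaction test that has no single effect estimate attached.

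The stake is interpretation. Both arms are prescribed the same energy deficit, and TRF is presented as changing when women eat rather than how much. If the TRF arm loses more weight, readers will ask whether those women simply ate less. An imprecise intake comparison makes it easier to miss a real difference and to credit timing with an effect of lower intake.

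**Working it through.** **Plan's own figure.** The document gives no intake effect, SD or power, so there is nothing to reproduce. The sample size rests on body weight alone and plays no part here.

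**Inputs**
- n = 24 per arm: 30 per group less the stated 20% attrition, 30 × 0.8 = 24 (Sample size).
- Assumed, not in the document: SD s = 400 kcal/d for a 3-day mean (range 300–500); equal correlation r = 0.5 between occasions (range 0.3–0.7); a constant gap D = 250 kcal/d at weeks 4 and 8 and 0 at baseline.
- Two-sided 5% tests; power from the noncentral t or F distribution.

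**Step 1. What the main effect estimates.** With arm differences 0, D, D the average is (0 + D + D)/3 = 2D/3. For D = 250 this is 166.7 kcal/d. If the week-4 and week-8 gaps differ, the result is still two thirds of their mean; gaps of 0.5 and 1 give 1.5/3 = 0.50 against a mean of 0.75. A 20,000-run simulation in SD units (26 per arm) returned 0.533 for a true 0.8.

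**Step 2. Power at the base case**

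1. Group main effect. Variance factor (1 + 2r)/3 = 0.667. SE = 400 × √(2 × 0.667/24) = 94.3. Ratio 166.7/94.3 = 1.77. Power 41%.
2. Group-by-time. Noncentrality n(D/s)²/[3(1 − r)] = 24 × 0.625²/1.5 = 6.25, on 2 and 92 df. Power 59%.
3. Week-8 t test. SE = 400 × √(2/24) = 115.5. Ratio 250/115.5 = 2.17. Power 56%.
4. Mean of weeks 4 and 8, adjusted for baseline. Variance factor (1 + r)/2 − r² = 0.50. SE = 400 × √(2 × 0.50/24) = 81.6. Ratio 250/81.6 = 3.06. Power 85%.

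**Step 3. Sensitivity**

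| Setting (24 per arm) | Main effect | Group-by-time | Week-8 t test | Baseline-adjusted |
|---|---|---|---|---|
| Gap 250, SD 400, r 0.3 | 49% | 44% | 56% | 81% |
| Gap 250, SD 400, r 0.5 | 41% | 59% | 56% | 85% |
| Gap 250, SD 400, r 0.7 | 35% | 82% | 56% | 94% |
| Gap 250, all SD 300–500 and r 0.3–0.7 | 24–73% | 30–97% | 40–81% | 62% to over 99% |
| Gap 316, SD 400, r 0.5 | 59% | 80% | 76% | 97% |

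The 316 kcal/d row is for scale. At an assumed 7,700 kcal per kg, the planning difference of 2.3 kg over 56 days is 2.3 × 7,700/56 = 316 kcal/d (288 to 370 at 7,000 to 9,000 kcal per kg).

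The baseline-adjusted analysis was highest in every setting, with near-ties only close to 100%. Group-by-time is not a reliable rescue: at r = 0.3 it is slightly weaker than the main effect.

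**The case against.** **The protocol never names the main effect.** This stands. When baseline is one of the levels, group-by-time is the usual between-arm test, and its change contrast recovers D in full. The end-of-study t test, if it also applies to intake, is not diluted either. A reader might infer that the plan shrinks the intake difference by a third; the document supports that only for one permitted reading.

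**A null intake finding is not the likely result.** This largely stands. At 316 kcal/d detection is more likely than not under the main effect (59%), group-by-time (80%) and the t test (76%). At 250 kcal/d, SD 400 and correlation 0.5, only the main effect falls below one half. All these figures rest on assumed inputs.

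**The three-time recalls are not the only intake evidence.** This stands. The Adherence section plans twice-weekly calls with a 24-hour recall compared with the prescribed diet. Those recalls serve adherence checking, and no between-arm analysis of them is stated.

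**Intake may not be the only variable measured three times.** Fair: follow-up times for anthropometry are not spelled out and the timeline figure is not shown. Intake is the only one with an explicit three-time schedule.

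**This is detail for an analysis plan.** Partly right. Silence on the tested term, or on incomplete recalls, is no fault in an article. But the section does choose the method, its three response levels and a covariate list. That stated choice can be improved, whichever term is meant.

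**Repeated ANOVA including baseline is valid and intake is not a listed outcome.** Both true. The point concerns precision and interpretation, not the validity of a primary or secondary test.

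**Conclusion.** The concern holds as a loss of precision. The pre-randomisation recall is a response level, baseline intake is not a listed covariate, and every intake comparison the section offers is weaker than one that uses weeks 4 and 8 together, adjusted for baseline. At the base case the adjusted analysis has 85% power against 41%, 59% and 56%. Those levels depend on the assumed SD, correlation and gap; the ranking held across the ranges tried.

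The one-third dilution is exact but conditional on the group main effect being the test. The document does not support saying that the intake difference will be shrunk, or that the trial will probably miss lower intake in the TRF arm. No listed outcome is biased; the consequence is weaker evidence on whether a weight difference reflects timing or lower intake.

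**What to change.** In Statistical analysis, replace the repeated ANOVA for dietary intake with a mixed model of the week-4 and week-8 values, with arm, visit, arm-by-visit and baseline intake as covariate. Keep women who have only one follow-up recall. Report the baseline-adjusted between-arm difference in energy intake over weeks 4 to 8, with its 95% CI, beside the weight result, and state that a non-significant difference will not be read as equal intake.

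The cost is a sentence or two of wording. The recalls are already scheduled, the named software can fit the model, and neither participants nor sample size are affected. The article reports that the trial was still enrolling, so the change can be made before analysis.

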### Plans for auditing trial conduct

There will be unplanned checks on the quality of the data or the progress of the trial.

### Ethical considerations

Women with overweight/obesity and food addiction who meet the inclusion criteria will be completely informed about the protocol of the study. The protocol of this study was approved by ethics committee of Shahid Beheshti University of Medical Sciences and is in conformity with the declaration of Helsinki (approved number IR.SBMU.NNFTRI.REC.1399.03).

### Protocol amendments

Any modifications to the protocol which may impact on the conduct of the study, potential benefit of the patient, or may affect patient safety, including changes of study objectives, study design, patient population, sample sizes, study procedures, or significant administrative aspects will require a formal amendment to the protocol. Such amendment will be agreed upon by NNFTRI (National Nutrition and Food Technology Institute) and approved by the ethics committee of Shahid Beheshti University of Medical Sciences prior to implementation. Administrative changes of the protocol are minor corrections and/or clarifications that have no effect on the way the study is to be conducted. These administrative changes will be agreed upon by NNFTRI. The ethics committee of Shahid Beheshti University of Medical Sciences may be notified of administrative changes at the discretion of NNFTRI.

## Discussion

Emerging evidence suggests that intermittent fasting has favorable effects on metabolic health and weight management [19]. A TRF is a kind of intermittent fasting that restricts eating window to less than 12 h per day [19]. It is suggested that TRF helps with reducing body weight, fasting blood sugar, systolic blood pressure, and blood lipids. Some studies suggest that TRF can also alter the gut microbiota [19].

LPS, as an endotoxin and inflammation marker with short half-life, is produced and released to blood circulation by gut microbiome and binds to LBP. High levels of LPS and LBP is representative of altered gut microbiome [24, 25].

Food addiction is one of the behavioral factors that is associated with adiposity and failure in lifestyle changes for weight loss [2–4]. People with higher stress levels are expected to be more susceptible to food addiction [22, 23]. In 2018, Bistoletti et al. suggested that dysbiosis can affect BDNF levels differently in ENS and CNS [35]. Alteration in BDNF levels can be associated with eating behavior and weight management [12] and previous studies on mice showed that compounds produced by gut microbiomes can alter brain levels of BDNF [13–16].

Based on previous studies, it seems that alteration in BDNF levels as a result of alteration in gut microbiota caused by TRF may be a novel strategy for management of food addiction and obesity. So, the aim of this study is to investigate the effect of TRF on anthropometric measures, eating behavior, stress, and serum levels of BDNF and LBP in women with overweight/obesity and food addiction.

## Trial status

This trail is in the enrolment stage.

Protocol version 2, 5/18/22.

Recruitment began on November 2021 and is expected to be completed on December 2023.

## Data Availability

Not applicable.

## Abbreviations

BMI: Body mass index
TRF: Time-restricted feeding
LBP: Lipopolysaccharide-binding protein
BDNF: Brain-derived neurotrophic factor
